### Ethical considerations

This study will be conducted in accordance with the protocol and in accordance with :

- The declaration of Helsinki of 1964.
- The international rules and regulations governing GCP (1996)
- The charter on ethical research in developing countries edited by the ANRS (May 2002)

### Informed consent

The patients will be informed in a transparent and complete fashion, in layman’s terms, of the objectives and constraints of the study, of the potential risks associated with the study, of the monitoring, of the patient’s right to decide not to participate in the study and of the patient’s right to withdraw from the study at any time in the future. All this information will be contained in the patient information sheet in the same document as the informed consent form. A written informed consent by the patients will be collected by the investigator, or a medical representative of the investigator, before recruitment into the study. A copy of the patient information sheet and of the signed informed consent form, signed by both the patient and the investigator, or the investigator’s representative, will be given to the patient, the investigator keeping one of the original copies. At the end of the study, one copy of this information sheet and consent form will be placed in a sealed envelope including all the other signed informed consent forms of the patients recruited into the study, and this envelope will be archived.

### Access to study data and source documents

Patients’ data collected during the study will be kept strictly confidential and anonymous. For audit purposes, only the medical and scientific representatives,

involved in the conduct of the study, in addition to a representative person from the health authority will be allowed to access the patients’ medical source data.

### Quality control and Quality assurance

In accordance with Good clinical practice (GCP), and in order to guarantee the quality of the study and protect the patients recruited in the study,each investigator of the study will commit to

- The regular monitoring and audit of the study.
- An eventual audit of the study, conducted by relevant organisations
- An audit of the study by the health authorities.

Guidance and monitoring plans will be written and communicated to the investigators. A CRF will be assigned to each patient recruited in the study, with a study number and the code linking this study number to the identification of the patient.

### Retention of the documents and data related to the study

The investigators in the study will archive the documents related to the study, and will keep these documents available for any potential audit for at least 15 years.

Such documents related to the study are as follows:

- updated version of the protocols, appendices, with any amendments.
- CRF
- Informed consent signed by the patients and the confidential list of patients having taking part in the study, linking each patient to the study number and the patient’s source hospital case notes.
- Correspondence related to the study

The source data file must be available for a period of 15 years.

### Patient Analysis Sets

- 1. **Main Analysis Set**

The Main Analysis Set is defined as the set of subjects who fulfilled the criteria as defined in the main inclusion criteria of the study, after confirmation by the

Adjudication Committee. Note that the special groups (see Section 3.3) included in the study are excluded from the Main Analysis Set.

### Full Analysis Set

The Full Analysis Set (FAS) is defined as the set of subjects who were included into the study.

### DILIN Patient Analysis Set

The DILIN Patient Analysis Set is defined as the set of subjects who fulfilled the criteria of the prospective US study group DILIN [5] criteria at D0 with published severity scales [6].

Inclusion laboratory criteria are a serum AST or ALT > 5 times ULN (or pretreatment baseline if baseline levels are elevated) on two separate occasions. Alternatively, subjects with serum alkaline phosphatase levels > 2 times ULN (or baseline if the baseline level is abnormal) on two consecutive occasions may qualify. In addition, subjects who develop a serum total bilirubin of greater than 2.5-mg/ dL or an INR above 1.5 in the absence of a competing cause of hyperbilirubinaemia or hypoprothrombinaemia, respectively.

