### Criteria for inclusion

Consecutive patients with suspected acute DILI as defined by:

1. ALT activity exceeding 3 x ULN or ALP > 2 x ULN, within the last 4 weeks before the baseline visit
2. When pre-treatment ALT or ALP activity is available and > ULN, an increase of at least 2-fold the pre-treatment level to D0 is required
3. History of drug intake including any prescription drug, over-the-counter drug, recreational drugs (cocaine, ecstasy, amphetamines), herbal medications and food supplements during the 6-12 months prior to the DILI onset,
4. Absence of other known causes of liver injury
5. Patients with age >18 years that are capable of and willing to provide written informed consent

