### Data collection

Medical and personal data will be collected at each time-point. All these data will be recorded within the framework of the SAFE-T consortium and entered into a personal file in the test centre and saved electronically. All medical and personal data collected will be kept under strict confidentiality at the responsibility of the SAFE-T consortium. The patient’s name will never be attached to those data (completely anonymous).

1. The following data will be collected at baseline:

- Inclusion/exclusion criteria
- Diagnosis of concomitant diseases
- Screen for HAV (anti-HAV), HBV (HBs-Ag, anti-HBc or PCR), HCV (anti-HCV or PCR), HIV (anti-HIV), and HEV (anti-HEV or PCR).
- Demography, smoking history
- Liver ultrasound and Fibroscan if available.
- At least self declaration of alcohol consumption, and if justified, alcohol test (Carbohydrate Deficient Transferrin, alcohol serum concentration), drug screen and pregnancy test
- Complete blood count
- Coagulation profile (PTT, INR, TPT)
- Clinical Chemistry (total protein, albumin, BUN/urea, creatinine, ferritin, transferrin, uric acid, cholesterol, triglycerides, glucose, HbA1C, calcium, magnesium, phosphorus, sodium, potassium, chloride, bicarbonate, amylase and lipase, creatine kinase (CK), CK-MB)
- Urine Analysis (Quantitative spot urine for protein, microalbumin, and creatinine Urinalysis consisting of color &clarity, specific gravity, pH, protein, glucose, ketones, bilirubin, urobilinogen, blood, nitrite, leukocyte esterase, Urine microscopic WBC, WBC)
- Thyroid Function (TSH)

1. The following data will be collected at each time-point (including baseline):

- Current medical conditions (symptomatology, date of onset of symptoms, interval between start of medication use and liver dysfunction)
- Medication in use during the last six months before admission (date of start and dosage of medications. Use of recreational drugs and herbals)
- Physical examination including body weight, height , blood pressure and heart rate.
- Clinical Chemistry (ALT, AST, GGT, LDH, total, direct/indirect bilirubin, alkaline phosphatase, creatinine, and uric acid).
- Exploratory biomarkers, including biomarkers for FibroTest/ActiTest

1. In addition, ALT and total bilirubin may be as Pre-treatment measurement and First-on-drug measurement (prior to D0).

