### DILI Patient Analysis Set

The DILI Patient Analysis Set is defined as the set of subjects who satisfied the latest consensus criteria for DILI definition at D0 [7].

ALT > 5 X ULN or

- ALP > 2 X ULN or
- ALT > 3 X ULN and TB > 2 X ULN.

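### The DILIN set must be met at D0, a single day, yet needs two measurement occasions; the DILI set can be derived but loses patients who met its thresholds before D0

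*Protocol*

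**What the plan says.** **DILIN set (Protocol Section 5.3).** Members are subjects who fulfilled the "criteria of the prospective US study group DILIN [5] criteria at D0 with published severity scales". The laboratory conditions are AST or ALT above 5xULN ("or pretreatment baseline if baseline levels are elevated) on two separate occasions"), or alternatively ALP above 2xULN ("or baseline if the baseline level is abnormal) on two consecutive occasions may qualify"). A further sentence mentions "subjects who develop a serum total bilirubin of greater than 2.5-mg/ dL or an INR above 1.5" without a competing cause. It has no main verb and no time attached.

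**DILI set (Section 5.4).** This is "the set of subjects who satisfied the latest consensus criteria for DILI definition at D0". It has three alternatives, each judged on single values: ALT above 5xULN; ALP above 2xULN; or ALT above 3xULN together with total bilirubin above 2xULN.

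**Entry (Section 3.2).** The first inclusion criterion is "ALT activity exceeding 3 x ULN or ALP > 2 x ULN, within the last 4 weeks before the baseline visit".

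**What D0 is.** Section 1.7.3 makes it the day of study admission and signed consent. Section 3.6.3 makes baseline the day of the first SAFE-T sample. Each is one day.

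**What is recorded.** The data collection list in Section 3.6.3 has ALT, AST, ALP and bilirubin at every time point including baseline. INR appears only among the baseline items. For earlier values it says "In addition, ALT and total bilirubin may be as Pre-treatment measurement and First-on-drug measurement (prior to D0"). Sections 1.7.1 and 1.7.2 describe such values as rarely or sometimes available, and as likely to be limited to ALT and total bilirubin.

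**The concern.** The DILIN definition contradicts itself: a condition that needs two occasions is tied to a day that supplies one. A programmer following it literally would put nobody in the set through the enzyme limbs. A programmer who relaxes it must choose a window that the protocol does not give, and then depends on laboratory values that the protocol does not list for collection.

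The DILI set has a different and lesser problem. Entry looks back 4 weeks while membership looks only at D0. A patient who met the consensus thresholds when the injury was found, and improved before consent, is enrolled but left out of the set. Fast improvers are the likeliest to be lost. Because the primary endpoint is full recovery at W12, which includes ALT below 2xULN, membership is plausibly related to outcome. A biomarker result in this set could then differ from the main result partly because of how late patients were sampled.

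**Working it through.** The protocol states no size for either set and no figure that can be reproduced here. The check sets the definitions against the data available, and adds an illustration.

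**1. DILIN enzyme limbs, read literally.** Occasions supplied by D0: 1. Occasions required: 2 for AST/ALT and 2 for ALP. Neither limb can be met.

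**2. DILIN enzyme limbs, read as by D0.** A second occasion must come from before D0.

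| Limb | D0 value listed | Pre-D0 value listed | Result |
|---|---|---|---|
| ALT > 5xULN, twice | yes | yes, where available | possible for some patients |
| AST > 5xULN, twice | yes | no | no planned second value |
| ALP > 2xULN, twice in succession | yes | no | only if the ALP value used for entry is captured |

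The listed on-drug item is the first measurement during treatment. Section 1.7.2 says that this will often be the D0 measurement itself, in which case there is still only one occasion. Membership would therefore depend largely on whether an earlier value happened to be recorded.

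**3. Bilirubin/INR sentence.** Both quantities are collected at baseline, so a D0 version could be programmed. The text does not say by when the rise must have developed, or whether it is a separate route or an added condition.

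**4. DILI set.** ALT, ALP and total bilirubin are all measured at D0, so every alternative can be evaluated. The open question is the lag between the qualifying value (up to 28 days earlier) and D0.

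**5. Illustration for the ALT-only alternative.** Assume that ALT halves every h days, with h = 7 and a range of 3 to 14. This is an assumption and not a protocol figure. For ALT to exceed 5xULN on D0, the value L days earlier must have exceeded 5 x 2^(L/h).

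- L = 7: 5 x 2^(7/7) = 10xULN; h = 14 gives 7.1 and h = 3 gives 25.
- L = 14: 5 x 2^(14/7) = 20xULN; h = 14 gives 10 and h = 3 gives 127.

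Turned round, the time to fall from m xULN to 5xULN is h x log2(m/5). From 10xULN this is h days (7; range 3 to 14). From 20xULN it is 2h days (14; range 6 to 28). These times lie within the 28-day entry window, so losing such a patient before D0 is possible. The patient leaves the set only if neither the ALP alternative nor the joint ALT and bilirubin alternative is met at D0. The illustration shows that loss can occur; it does not estimate how many patients are lost.

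**The case against.** Several stronger conclusions are tempting, and the protocol does not support them.

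- **That neither set can be derived.** This is untrue of the DILI set, which uses single values all measured at D0. For the DILIN set it is certain only on the literal reading; read as by D0, some patients can be classified on ALT.
- **That the DILIN set requires events after D0.** The verb in the bilirubin/INR sentence invites that inference, but no time is stated. It is an unfinished sentence and not a post-baseline requirement.
- **That the AST and ALP routes are closed.** Sections 1.7.1 and 1.7.2 say only that earlier data are likely to be limited to ALT and bilirubin, and entry itself uses ALP from before the baseline visit. The first limb accepts either AST or ALT, so missing AST does not close it.
- **That any difference from the Main Analysis Set would be a sampling artefact.** Entry needs ALT above 3xULN, while the ALT-only limbs of these sets need more than 5xULN. A patient peaking at 4xULN with no raised bilirubin or ALP is meant to fall outside the DILI set, whatever the delay.

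It can also be argued that D0 is a coherent anchor, since the primary objective concerns biomarkers measured from baseline. For some patients the lag will be zero, and Section 7 assigns no specific analysis to either set. These points limit the importance of the problem. They do not remove the contradiction in Section 5.3, nor the loss of patients who did meet the stricter threshold on an earlier day. A SAP could choose another window only by departing from the protocol's stated day, and it could not supply laboratory values that were never collected.

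**Conclusion.** The point stands in a limited form. Section 5.3 cannot be applied as written: its enzyme limbs need two occasions on a one-day criterion, and its last sentence is incomplete. Reading it as by D0 rescues it only for patients with a recorded earlier value.

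Section 5.4 can be applied, but its D0-only test does not match the 4-week entry window, so some patients who met the consensus thresholds before consent drop out. How many cannot be computed from the protocol; the figures above rest on assumed halving times and lags. Part of any difference from the Main Analysis Set is the intended stricter threshold.

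The Main Analysis Set follows the inclusion criteria and is unaffected. This should be corrected because the rule fails as written and the repair is cheap, not because the primary result is at risk.

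**What to change.** **Section 5.3.** Replace the D0 condition with two measurements on separate days from 4 weeks before D0 up to and including D0, keeping the requirement that the ALP values be consecutive. Complete the bilirubin/INR sentence with the same window, and say whether it is a separate route or an added condition.

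**Section 5.4.** Apply the thresholds on any date in that same window. For the joint criterion, take ALT and total bilirubin from the same date; separate maxima could combine values from different days and change the definition. Keep the D0-only version as a sensitivity set.

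**Section 3.6.3.** Add dated pre-D0 AST, ALP and INR values from the medical record to the data collection list, beside ALT and total bilirubin.

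**Do not use post-D0 values for membership.** Taking the second occasion from D1 to W1, for example, would select patients whose enzymes stay raised, using information from follow-up. It would also miss patients whose mandatory second sample, allowed from day 5 to week 2, falls on days 8 to 14.

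**Cost.** Wording in two sections and a few extra data fields. Patients without a second pre-D0 value for the enzyme limbs, and not classifiable otherwise, must be counted and reported as unclassifiable for the DILIN set and not treated as failing it.

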### DILI Patient Analysis Set

The DILI Patient Analysis Set is defined as the set of subjects who satisfied the latest consensus criteria for DILI definition at D0 [7].

ALT > 5 X ULN or

- ALP > 2 X ULN or
- ALT > 3 X ULN and TB > 2 X ULN.

### Endpoints

### Primary Endpoint: Binary Recovery Outcome

The primary endpoint is the category 1 recovery outcome (see Section 1.6.1), that is the "full" recovery at the last visit (W12).

### Secondary Endpoints: Categorical Recovery Outcome

The recovery outcome with 3 ordered categories [1] full recovery, [2] partial recovery including adaptive response and [3] not recovered including severe complications **(see Section 1.6.1)** will be defined as a secondary outcome with normal ranges used as defined in Section 1.7.4.

### Secondary Endpoints: Binary Outcomes

A series of binary outcome variables will be defined by an indicator set to one if the following criteria are met and zero otherwise.

### Severe Biochemical DILI

A patient will be deemed to have “severe biochemical DILI” if the patient has:

- An increase in total serum bilirubin of at least 10 umol/l more than the baseline value (D0); or
- An elevation of total bilirubin to 34 umol/l (Hy's law) at any other measurements between D1 to W12;

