### Normal Ranges

Normal ALT will be defined in IU/L for men and women, after centralization of 30 random samples of each participating centers to avoid variability in analytic conditions or definition of ULN (statistical definition or control group characteristics). The 30 samples per liver center will be taken at the Biobank and sent for blind analysis to the Pitié Salpêtrière Biochemistry department.

Normal total Bilirubin will be defined as <= 17 umol/l. If a proved Gilbert syndrome is present or other patent cause of unconjugated hyper bilirubinemia (e.g. hemolysis), the conjugated bilirubin will replace the total bilirubin.

No sign of significant liver fibrosis will be defined as FibroTest <=0.48 between 8 to 12 weeks. Unreliable results will be those defined by the BioPredictive algorithms

and reported in the result sheet. If FibroTest results are not reliable according to the company security algorithms, Fibroscan results can be used, with the predetermined standard cut-off <7.1 kPa for the absence of advanced fibrosis.

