### Secondary Objectives

The new biomarkers will be compared to ALT and total bilirubin, which are the "Standard of Diagnosis" (including Hy's Law), and to ActiTest which is already commercially available for the secondary objectives:

- - - Investigate the performance of investigational biomarkers from baseline D0 to Week 12) to predict:

1. A subsequent increase in total serum bilirubin of at least 10 umol/l more than the baseline value (D0) or an elevation of total bilirubin to 34 umol/l (Hy's law is TBILI 2xULN together with ALT 3xULN) at any other measurements between D1 to W12;
2. Death or severe liver complications (including transplant and complications associated with liver failure such as: hepatic encephalopathy, hemorrhage, associated liver failure complications: kidney failure, medical ventilation, circulatory dysfunction and infections.
3. Type of liver injury (hepatic, cholestatic and mixed).
4. Time to discharge from hospital.
   - - For each of the outcomes in (i) to (iii) determine the best investigational biomarker with associated thresholds.
     - For each of the outcomes in (i) to (iii) determine the best combination of biomarkers with associated threshold.
     - Type of drugs suspected in DILI will be assessed.
     - The prevalence of associated liver risk factors such as alcohol consumption, metabolic factors, history of familial liver disease, history of drug adverse events, history of recreational drugs (cocaine, ecstasy, amphetamines), combination of different drugs and herbals will be assessed and may be incorporated into statistical models.

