### Secondary Endpoints: Time to Events

The time from D0 to reaching the following outcomes will be calculated:

1. Full Recovery from DILI;
2. Severe biochemical DILI
3. Severe clinical DILI (i.e. death or liver complications/failure).

Where a patient does not meet the criteria of the outcome, a censored time will be used as the time of last follow-up visit.

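### The 34 umol/l limb of severe biochemical DILI has no D0 condition, so patients already jaundiced and improving can count as events, which tilts this secondary outcome towards D0 bilirubin

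*Protocol*

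**What the plan says.** Section 6.3.1 of the protocol defines severe biochemical DILI by two limbs joined by an or. The first is relative to entry: "An increase in total serum bilirubin of at least 10 umol/l more than the baseline value (D0); or". The second is a level: "An elevation of total bilirubin to 34 umol/l", labelled there as Hy's law and applied to any measurement from D1 to W12.

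Section 2.2 states the same outcome as a prediction target: "A subsequent increase in total serum bilirubin of at least 10 umol/l more than the baseline value (D0) or an elevation of total bilirubin", with the same 34 umol/l level. It adds in brackets that Hy's "law is TBILI 2xULN together with ALT 3xULN". Section 6.4 makes "Severe biochemical DILI" a time-to-event endpoint counted from D0.

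Four other provisions bear on the point:

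- **Normal range (1.7.4):** "Normal total Bilirubin will be defined as <= 17 umol/l".
- **Entry (3.2):** the laboratory criterion is ALT above 3 x ULN or ALP above 2 x ULN. D0 bilirubin has no upper limit.
- **Analysis sets (5.1 to 5.4):** none removes patients with high D0 bilirubin. Section 5.4 lists bilirubin above 2 x ULN at D0, with ALT above 3 x ULN, as one way to qualify.
- **Comparators (2.1, 2.2, 7.1):** new markers are compared with ALT and total bilirubin, and AUROCs are produced for both.

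**The concern.** The second limb does not ask whether bilirubin was already at 34 umol/l when the patient entered. D0 may be the first day of hospitalization for DILI (1.7.3), so some patients will be jaundiced at entry. For them the limb records persistence, not a new event. Whether it is met then depends largely on the D0 bilirubin value, and bilirubin is one of the markers being judged.

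Three pieces of planned work are affected: the AUROC comparison of new markers with total bilirubin; the choice of best marker, combination and threshold that 2.2 promises for this outcome; and the time-to-event analysis, in which such patients have their event at the first post-D0 sample still at or above 34. Selection would reward markers that track existing jaundice as well as those that foresee deterioration.

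**Working it through.** **1. The threshold.** ULN is 17 umol/l (1.7.4), so 2 x 17 = 34 umol/l. The protocol's figure reproduces.

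**2. Whom the second limb adds.** If D0 is 24 or less, reaching 34 is a rise of at least 34 - 24 = 10, which the first limb already counts. The second limb therefore changes a classification only when D0 exceeds 24. Between 24 and 34 it adds small new crossings. From 34 upwards it adds patients who have not risen by 10 but are still at or above 34.

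**3. One patient.** Assume D0 = 100 umol/l and a half-life of 7 days. Then 100 x 2^(-1/7) is about 91 on D1, 100 x 2^(-3/7) about 74 on D3, and 100 x 2^(-1) = 50 at W1. Bilirubin falls throughout, yet the patient is an event at the first sample taken on any of these days.

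**4. How high D0 must be.** An improving patient is still at 34 on day d if D0 is at least 34 x 2^(d/half-life).

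| First post-D0 sample | Half-life 5 days | 7 days | 14 days |
|---|---|---|---|
| D1 | 39.1 | 37.5 | 35.7 |
| D3 | 51.5 | 45.8 | 39.4 |
| W1 | 89.7 | 68.0 | 48.1 |

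**5. Closed-form check.** Let p be the share with D0 at or above 34 and w the share truly worsening, independent of D0. Assume every patient in p is still at or above 34 at the first sample.

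- Event rate = p + (1 - p)w
- Improving share of events = p(1 - w) / event rate
- AUROC of D0 bilirubin = 1 - 0.5 x (1 - p)w / event rate

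With p = 0.10 and w = 0.15: event rate 0.10 + 0.135 = 0.235; improving share 0.085/0.235 = 36%; AUROC 1 - 0.5 x 0.135/0.235 = 0.71. With p = 0.50 and w = 0.15: event rate 0.575; improving share 0.425/0.575 = 74%; AUROC 1 - 0.5 x 0.075/0.575 = 0.93.

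**6. Simulation with falling bilirubin.** 200,000 patients per scenario. All inputs are assumptions: D0 log-normal with median 17, 34 or 68 umol/l and log-SD 1.2 (28%, 50% or 72% at or above 34); decline towards 5 umol/l with median half-life 7 days; 5%, 15% or 30% truly rising by at least 10, independent of D0; first post-D0 sample at D1 or W1. Cells show event rate / improving share of events / AUROC of D0 bilirubin.

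| D0 median | Worsening | First sample D1 | First sample W1 |
|---|---|---|---|
| 17 | 5% | 29% / 83% / 0.94 | 18% / 71% / 0.87 |
| 17 | 15% | 37% / 59% / 0.85 | 26% / 43% / 0.75 |
| 17 | 30% | 48% / 37% / 0.77 | 39% / 24% / 0.67 |
| 34 | 5% | 49% / 90% / 0.97 | 32% / 85% / 0.93 |
| 34 | 15% | 55% / 73% / 0.93 | 40% / 62% / 0.85 |
| 34 | 30% | 63% / 52% / 0.87 | 50% / 40% / 0.78 |
| 68 | 5% | 71% / 93% / 0.99 | 52% / 90% / 0.95 |
| 68 | 15% | 74% / 80% / 0.97 | 57% / 74% / 0.91 |
| 68 | 30% | 78% / 62% / 0.94 | 65% / 54% / 0.86 |

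When the second limb is limited to D0 below 34, the event rate returns to the assumed 5%, 15% or 30% and the AUROC to about 0.50. Both follow from the set-up: worsening was made independent of D0, and small crossings from 24 to 34 were not modelled. The excess over 0.50 is the part produced by the definition.

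**The case against.** **The wording may mean a new rise.** An elevation to 34, at other measurements, under a sentence in 2.2 that begins with a subsequent increase, could describe a new crossing. The two limbs would still do separate work: 30 to 35 meets only the second, and 15 to 26 or 100 to 115 only the first. This reading is possible, but neither section states it, and the D0 reference is attached only to the first limb. An analyst who programs the text as it stands will count improving patients. The SAP may clarify this, but the protocol fixes the definition.

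**The label says severe, not worsening.** A bilirubin of 80 on D1 is high by any description. That is fair for describing severity. It does not help an outcome that 2.2 sets up for prediction, with bilirubin among the predictors compared.

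**The size is assumed.** This stands. The protocol gives no D0 bilirubin distribution. Section 3.6 says the required numbers are unlikely if only Hy's law cases are used, so patients with both elevations may be a minority; at 10% the AUROC above is 0.71. If worsening is positively associated with D0 bilirubin, the gap from a properly defined outcome narrows.

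**Events need not pile up at D1.** This stands too. Section 3.6.3 makes only three samples mandatory, the first after D0 between day 5 and week 2. The outpatient blood volume is 168/24 = 7 draws against 216/24 = 9. With a 7-day half-life, a patient first resampled on day 5 is an event only if D0 is at least 34 x 2^(5/7) = 56.

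**Conclusion.** The definition in 6.3.1, repeated in 2.2 and carried into 6.4, lacks a D0 condition on its 34 umol/l limb. Read literally, it tilts this secondary outcome towards D0 bilirubin and against new markers. The direction follows from the text. The size does not: the AUROC range of about 0.67 to 0.99 and the improving share of about 24% to 93% rest on assumed D0 distributions, decline rates, sampling times and independence of worsening from D0.

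A reader might infer more than the protocol supports:

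- **That the endpoint mostly records entry jaundice, with a near-perfect AUROC for bilirubin.** This holds in some scenarios and not in others.
- **That no new marker could show added value.** In many scenarios the AUROC leaves headroom, ALT is a comparator as well, and 7.1 allows combinations. The comparison is tilted, not closed.
- **That event times collapse to D1.** They fall on the first post-D0 sample still at or above 34, whose timing varies.
- **That the Hy's law wording is a second source of bias.** The bilirubin trigger is 34 umol/l in both sections. It is a labelling inconsistency: 6.3.1 attaches the name to bilirubin alone, while 2.2 says it also involves ALT.

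The primary endpoint, full recovery at W12, does not use this definition and is unaffected. The change should be made, as a correction to a secondary endpoint.

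**What to change.** In 2.2, 6.3.1 and 6.4, state that the 34 umol/l limb counts only for patients with D0 bilirubin below 34 umol/l, as a new crossing after D0. Keep the rise of at least 10 umol/l for all patients. Optionally report results separately for D0 bilirubin below 34 and at or above 34.

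Separately, reconcile the Hy's law label in 6.3.1 with its description in 2.2.

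The cost is about one sentence in each section, and no new data are needed. There will be fewer events on this outcome and wider confidence intervals. The rule also creates a discontinuity at the threshold: 33 to 34 counts as an event, while 35 to 44, a rise of 9, does not. That should be acknowledged where the endpoint is defined.
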